# Affect school and script analysis versus basic body awareness therapy in the treatment of psychological symptoms in patients with diabetes and high HbA1c concentrations: two study protocols for two randomized controlled trials

**DOI:** 10.1186/s13063-016-1347-8

**Published:** 2016-04-27

**Keywords:** Alexithymia, Anxiety, Cortisol, Depression, Diabetes mellitus, HbA1c, Mind-body therapy, Randomized controlled trial, Psycho-education

## Abstract

**Background:**

Depression is linked with alexithymia, anxiety, high HbA1c concentrations, disturbances of cortisol secretion, increased prevalence of diabetes complications and all-cause mortality. The psycho-educational method ‘affect school with script analysis’ and the mind-body therapy ‘basic body awareness treatment’ will be trialled in patients with diabetes, high HbA1c concentrations and psychological symptoms. The primary outcome measure is change in symptoms of depression. Secondary outcome measures are changes in HbA1c concentrations, midnight salivary cortisol concentration, symptoms of alexithymia, anxiety, self-image measures, use of antidepressants, incidence of diabetes complications and mortality.

**Methods:**

Two studies will be performed. Study I is an open-labeled parallel-group study with a two-arm randomized controlled trial design. Patients are randomized to either affect school with script analysis or to basic body awareness treatment. According to power calculations, 64 persons are required in each intervention arm at the last follow-up session. Patients with type 1 or type 2 diabetes were recruited from one hospital diabetes outpatient clinic in 2009. The trial will be completed in 2016. Study II is a multicentre open-labeled parallel-group three-arm randomized controlled trial. Patients will be randomized to affect school with script analysis, to basic body awareness treatment, or to treatment as usual. Power calculations show that 70 persons are required in each arm at the last follow-up session. Patients with type 2 diabetes will be recruited from primary care. This study will start in 2016 and finish in 2023. For both studies, the inclusion criteria are: HbA1c concentration ≥62.5 mmol/mol; depression, alexithymia, anxiety or a negative self-image; age 18–59 years; and diabetes duration ≥1 year. The exclusion criteria are pregnancy, severe comorbidities, cognitive deficiencies or inadequate Swedish. Depression, anxiety, alexithymia and self-image are assessed using self-report instruments. HbA1c concentration, midnight salivary cortisol concentration, blood pressure, serum lipid concentrations and anthropometrics are measured. Data are collected from computerized medical records and the Swedish national diabetes and causes of death registers.

**Discussion:**

Whether the “affect school with script analysis” will reduce psychological symptoms, increase emotional awareness and improve diabetes related factors will be tried, and compared to “basic body awareness treatment” and treatment as usual.

**Trial registration:**

ClinicalTrials.gov: NCT01714986

## Background

Diabetes is a progressive and demanding chronic disease, which might cause secondary distress requiring emotional adaptation [1]. An increased prevalence of depression is found in patients with diabetes [2, 3]. The comorbidity is linked with inadequate glycemic control [4], disturbances in cortisol secretion [3, 5], increased prevalence of diabetes complications [6, 7] and all-cause mortality [7].

Affects are the innate, unconscious and strictly biological portions of emotions [8–12]. Deficits in the awareness of affects result in abnormal physiological reactions and impaired capacity for self-care and self-regulation [13]. Alexithymia includes difficulties in identifying and describing feelings, as well as low capacity for introspection and reflection [13, 14]. Alexithymia has been demonstrated as a risk factor of depression but the number and prevalence of alexithymic features might also increase during depressive episodes [15]. Type 1 diabetes [16], inadequate glycemic control of diabetes [17], reflexive emotional eating and obesity [18–20] and increased cardiovascular mortality [21] have been linked to alexithymia. Anxiety has been associated with depression [4] and inadequate glycemic control [22].

A negative self-image, which includes self-hate, self-ignorance or self-blame, is often present in persons with eating disorders [23], which, in turn, are associated with inadequate glycemic control [24].

High concentrations of HbA1c [25, 26] and disturbances in cortisol secretion [27, 28] are linked to complications of diabetes.

The psycho-educational method ‘affect school with script analysis’ (ASSA) was constructed by Bergdahl and Armelius [29, 30], inspired by Silvan S. Tomkins’ affect theory [8–11] and its interpretation by Nathanson [12] and Monsen and Monsen [31]. This method has previously been shown to decrease alexithymia [32] and stress symptoms [30].

‘Basic body awareness therapy’ (BBAT) is a physiotherapeutic mind-body therapy [33], where increased body awareness and increased integration between body and mind are key elements, as in other mind-body therapies such as Tai Chi, yoga, meditation and mindfulness-based therapies. In Sweden, BBAT is used in both psychiatric and primary care settings for treating psychiatric and somatic health issues [34–36].

### Objective and research questions

#### Studies I and II

The main hypothesis in these two studies is that an increased emotional awareness and verbal expressiveness might have beneficial health implications, such as lessening of depressive symptoms. The primary outcome measure is change in symptoms of depression. Secondary outcome measures are changes in symptoms of alexithymia, anxiety, self-image measures, HbA1 concentrations, midnight salivary cortisol concentration, use of antidepressants and incidence of diabetes complications and mortality.

#### Study I

The main aim is to compare the effects of ASSA and BBAT in patients with type 1 or type 2 diabetes, psychological symptoms and inadequate glycemic control.

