### Participants and procedure

#### Inclusion criteria for baseline analysis (Fig. ***1***)

These are outlined in Fig. 1. For Study I, participants must have either type 1 or type 2 diabetes. For Study II, participants must have type 2 diabetes. For both studies, participants must be aged 18–59 years, have had diabetes for at least 1 year and must provide signed informed consent.

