#### Randomization and allocation

The randomization and allocation of the coded patients will be performed by an independent statistician with the purpose of having as equal distribution as possible of sex and age in each intervention arm.

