##### Study I

This is outlined in Fig. 2. Patients who fulfilled the criteria were randomized into two intervention arms, ASSA (group 1) or BBAT (group 2). After allocation, the ASSA and BBAT instructors offered renewed oral information and patients made their final decisions regarding participation. Group 3 consists of patients who fulfilled the criteria but refused participation after allocation, and group 4 consists of patients who did not fulfil the criteria. Groups 3 and 4 will be followed as comparison groups.

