### Intention to treat analysis

#### Studies I and II

Differences at T0 between participants and nonparticipants fulfilling criteria will be analyzed regarding age, sex, self-reported depression and anxiety, alexithymia, self-image, clinical psychiatric diagnoses, smoking, physical inactivity, metabolic variables, medication and sick-leave status and will be thoroughly described. Levels of HbA1c will be determined for all patients who participate in the interventions, but decline to complete the questionnaires at T2, T3 (Study II only) or T4. At T4, all patients who participated at T0 will be asked for oral and written consent to participate in all the assessments, measurements and data collection that are included at T4. If full assessments are not possible we will collect data regarding HbA1c concentrations, mortality, diabetes complications and use of antidepressants.

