#### Study I

If we assume that the standard deviation for the individual changes in Hospital Anxiety and Depression Scale – depression subscale in this study is 2.8, a change of 1.4 points represents half the standard deviation, which is considered indicative of clinically relevant changes in subjective symptoms [52]. Calculating a statistical power of 80 %, and assuming significance at the 0.05 level, 64 persons in each intervention arm are required at follow-up in a two-arm randomized controlled trial. Unfortunately we only recruited around 21 persons in each arm in Study I, rendering a power of 37 %.

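### Study I pools type 1 and type 2 diabetes in arms of about 21, but neither the allocation nor the named arm test accounts for type: a small, cheaply removed loss of precision and conditional balance

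*Protocol article*

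**What the plan says.** Objective and research questions, Study I, sets the aim: "The main aim is to compare the effects of ASSA and BBAT in patients with type 1 or type 2 diabetes". Both types are eligible for Study I: "For Study I, participants must have either type 1 or type 2 diabetes" (Inclusion criteria for baseline analysis). Study II takes type 2 only. An independent statistician allocates patients "with the purpose of having as equal distribution as possible of sex and age in each intervention arm" (Randomization and allocation); diabetes type is not mentioned. On the achieved size, Power calculations for sample size, Study I, says: "Unfortunately we only recruited around 21 persons in each arm in Study I, rendering a power of 37" per cent.

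Statistical analysis, Study I, names the Wilcoxon signed rank test and the Kruskal-Wallis test for change in the self-reported symptoms and midnight cortisol. The part for both studies adds a paired t test for HbA1c, and linear and logistic regression of outcomes on baseline characteristics. Those characteristics are not listed, and arm is not named as a term.

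Two other places bear on the point. After allocation patients were informed again and made their final decision; "Group 3 consists of patients who fulfilled the criteria but refused participation after allocation" (Randomization and allocation, Study I). And Study design says that the results of the two studies will also be compared with each other.

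**The concern.** Diabetes type is known for every patient at entry and may be prognostic for several outcomes. The Background lists "Type 1 diabetes [16], inadequate glycemic control of diabetes [17" and other factors as linked to alexithymia, which is both an intervention criterion and a secondary outcome. HbA1c and complications are also secondary outcomes, followed for seven years. It is reasonable, though not stated in the article, to expect them to run differently in the two types.

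With arms of about 21, the mix of types can differ noticeably by chance. It can also differ because patients could refuse once they knew their arm, and the Discussion expects BBAT to be accepted more easily. An unstratified rank test does not correct a given difference in mix. In addition, if Study I is not shown by type, its comparison with the type 2-only Study II confounds diabetes type with setting (hospital clinic versus primary care).

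**Working it through.** **Inputs from the article.** SD of change on the HADS depression subscale 2.8; target difference 1.4 (0.5 SD); alpha 0.05 (two-sided assumed); 64 per arm planned; about 21 per arm achieved. **Assumed, because the article gives neither:** the type 1 share and the effect of type on change.

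**1. The plan's own figures.** The two-sample t test (noncentral t) at 64 per arm gives power 80.1 %, so 64 reproduces. At 21 per arm the normal approximation gives 36.7 %, matching the stated 37 %; noncentral t gives 35.3 %.

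**2. Chance of an uneven mix.** Let X1 and X2 be independent Binomial(21, p), with p the type 1 share. P(|X1 - X2| >= 5), where 5/21 = 23.8 percentage points:

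| p | 0.3 | 0.4 | 0.5 | 0.6 | 0.7 |
|---|---|---|---|---|---|
| P | 0.128 | 0.155 | 0.164 | 0.155 | 0.128 |

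If the total number of type 1 patients among 42 is held fixed instead (hypergeometric), the probability is about 18-22 % for odd totals and about 9-12 % for even totals; the binomial figures average over these.

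**3. Size of the shift.** Shift = imbalance x type effect. With 0.238 and an assumed type effect of 0.3-0.5 SD, it is 0.238 x 0.3 = 0.07 SD to 0.238 x 0.5 = 0.12 SD. On the depression subscale this is 0.238 x 0.84 = 0.20 to 0.238 x 1.4 = 0.33 points, against a target of 1.4 and a standard error of 2.8 x sqrt(2/21) = 0.86. So the shift is 14-24 % of the target and 0.23-0.39 of a standard error.

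**4. Error rate and power.** Simulation with 10,000 trials per setting, 21 per arm, half type 1, total SD 2.8:

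| Type effect (points) | Type I error, unadjusted rank test | Same, given imbalance of 5 or more | Power, unadjusted rank test | Power, linear model with arm and type |
|---|---|---|---|---|
| 0 | 4.8 % | 5 % | 33 % | 35 % |
| 0.7 (0.25 SD) | 4.9 % | 5 % | 33 % | 35 % |
| 1.4 (0.5 SD) | 4.8 % | 6 % | 33 % | 36 % |
| 2.8 (1 SD) | 4.7 % | 11 % | 33 % | 44 % |

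About 2 points of the gain come from changing the test, not from adding type. Compared with an unadjusted t test (35.3 %), adding type gains almost nothing until the type effect approaches a full SD.

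**5. Price of adjustment.** When 42 patients are allocated at random, the expected squared correlation between arm and type is 1/41. The standard error therefore rises by a factor of about 1/sqrt(1 - 1/41) = 1.012, roughly 1 %, if type has no effect at all.

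**The case against.** A reader might infer that a chance difference in type could pass for a therapy effect. The article does not support that for the primary outcome. A randomised comparison already allows for chance imbalance, and the overall error rate stays near 5 %. Even in the imbalanced trials it is about 5-6 % for type effects up to half an SD. It reaches 11 % only for a full-SD effect, and the article links type 1 diabetes to alexithymia, not to change in depression.

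Nor does the article show that type is left out of every analysis. Regression on baseline characteristics is planned, and for complications logistic regression is the only method given. The covariates may be listed in a full protocol or SAP that is not shown. What stands is narrower: the stated arm test is unadjusted, and the regression as described is not an arm comparison.

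Two further inferences should be avoided. The paired t test for HbA1c is a within-patient test, so it cannot be cited as an unadjusted arm comparison. The T0 list under Intention to treat analysis, which includes "clinical psychiatric diagnoses, smoking, physical inactivity, metabolic variables, medication and sick-leave status", compares participants with eligible nonparticipants; its silence on type says nothing about balance between arms. The final report is to follow CONSORT, under which a baseline table by arm would normally reveal an imbalance.

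Balancing on age may also partly balance type, if type 1 patients are younger (an assumption); the probabilities in step 2 would then be lower.

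**Conclusion.** The point holds as a minor improvement in precision and conditional balance, not as an error that invalidates Study I. A difference of 5 or more of 21 patients in type arises by chance in about 13-16 % of trials (type 1 share 30-70 %, simple randomisation). It moves the depression contrast by 0.20-0.33 points if type is worth 0.3-0.5 SD.

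The expected gain on the depression subscale is small. It may be larger for HbA1c if type is strongly prognostic there, which the article does not quantify. Selective refusal after allocation could widen the difference in type by an unknown amount. The 5 % error rate of a randomised test does not cover that, and adjusting for type would remove only the part carried by type. The main limit of Study I remains its disclosed power of 37 %.

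**What to change.** 1. In Statistical analysis (Study I, and Studies I and II), state that the Study I between-arm comparisons of change in HADS depression, TAS-20, cortisol and HbA1c are made either by a rank test stratified by diabetes type (van Elteren) or by a linear model with arm and type. Choose one per outcome in advance. Do not require this for complications, where events may be too sparse in about 42 patients.
2. Show the Study I results by diabetes type, descriptively, so that the planned comparison with Study II does not mix type with setting.
3. Add diabetes type to the characteristics compared between participants and eligible nonparticipants under Intention to treat analysis, so that selection by type among refusers is visible.

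The cost is wording plus one degree of freedom (standard error up about 1 % in a linear model). Type is already known from the entry criteria, and nothing changes for patients or visits.

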#### Study II

The main aim is to compare ASSA, BBAT with only treatment as usual in patients with type 2 diabetes, psychological symptoms and inadequate glycemic control.

## Methods/design

### Study design

These studies were registered with ClinicalTrials.gov on 24 October 2012 (NCT01714986). The final report will follow the CONSORT extension for non-pharmaceutical interventions.

Intervention with ASSA and BBAT will be tried in two studies with different study designs for patients with type 1 or type 2 diabetes, psychological symptoms and inadequate glycemic control in Region Kronoberg, Sweden. Results from the two studies will be presented separately but will also be compared.

#### Study I

This is an open-labeled parallel-group study with a two-arm randomized controlled trial design, which was initiated in 2009 and will be complicated in 2016 for patients with type 1 or type 2 diabetes recruited from one hospital diabetes outpatient clinic.

#### Study II

This is a multicentre open-labeled parallel-group study with a three-arm randomized controlled trial design, which will start in 2016 and will be completed in 2023 for patients with type 2 diabetes recruited from primary care units.

### Participants and procedure

#### Inclusion criteria for baseline analysis (Fig. ***1***)

These are outlined in Fig. 1. For Study I, participants must have either type 1 or type 2 diabetes. For Study II, participants must have type 2 diabetes. For both studies, participants must be aged 18–59 years, have had diabetes for at least 1 year and must provide signed informed consent.

**Fig. 1 Fig1:**
[figure not shown]
Description of criteria for randomization and allocation to ASSA (Studies I and II), BBAT (Studies I and II) and treatment as usual (Study II)

#### Exclusion criteria

These are outlined in Fig. 1. For both studies, exclusion criteria are:PregnancySevere comorbidities, if it is anticipated that participation would be difficult or unsafe for the patient (end-stage renal disease, cancer, hepatic failure, visual impairment to such a degree that reading questionnaires would be impossible, impaired hearing to such a degree that participation in discussions during the group sessions would not be possible, psychotic disorders, bipolar disorder, suicide ideation, severe personality disorder, or severe substance abuse)Cognitive deficiencies (mental retardation, stroke or dementia)Inadequate knowledge of Swedish.

#### Intervention criteria

For both studies, these are either a HbA1c concentration of at least 62.5 mmol/mol or at least one of: self-reported depression, anxiety, alexithymia or a negative self-image (Fig. 1).

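### The rule for randomisation makes high HbA1c and a psychological criterion alternatives, whereas the title, abstract, aims, design and summary describe patients with both

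*Protocol article*

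**What the plan says.** Under Intervention criteria, the protocol article gives one rule for both studies: "either a HbA1c concentration of at least 62.5 mmol/mol or at least one of: self-reported depression, anxiety, alexithymia" or a negative self-image. It refers to Fig. 1, which is not reproduced in the text at hand.

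Elsewhere the population is described differently:

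- Abstract, Methods, gives the inclusion criteria for both studies as one cumulative list: "HbA1c concentration ≥62.5 mmol/mol; depression, alexithymia, anxiety or a negative self-image; age 18–59 years; and diabetes duration ≥1 year".
- Abstract, Background, says the interventions "will be trialled in patients with diabetes, high HbA1c concentrations and psychological symptoms".
- Objective and research questions, Study I, sets the comparison "in patients with type 1 or type 2 diabetes, psychological symptoms and inadequate glycemic control".
- Objective and research questions, Study II, sets it "in patients with type 2 diabetes, psychological symptoms and inadequate glycemic control".
- Study design and the closing summary of the Discussion again name psychological symptoms together with inadequate glycemic control, and the title pairs psychological symptoms with high HbA1c.

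Under Randomization and allocation, patients who meet the criteria are randomised (two arms in Study I, three in Study II). Those who do not meet them form a separate group: group 4 in Study I and group 5 in Study II.

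**The concern.** The Intervention criteria section is the only part of the Methods that says how the HbA1c condition and the psychological condition combine, and it combines them in a way that the rest of the article does not. The difference decides membership of the randomised arms, and it also decides who is classed as ineligible and followed as a comparison group.

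Under the rule as written, a patient with HbA1c of 65 mmol/mol and no psychological criterion is randomised to an intervention aimed at psychological symptoms and is counted in the depression outcome. A patient with a psychological criterion and HbA1c below the cut-off is also randomised. By the abstract and aims, both belong in the ineligible group. At stake is which population the trial result describes. A report that describes patients with both conditions would be inaccurate if either condition alone had been enough for entry.

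**Working it through.** **1. The two rules side by side.** Cross-classify the patients who meet the baseline entry criteria by the two conditions. Let a, b, c and d be the proportions in the four cells.

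| HbA1c at least 62.5 mmol/mol | At least one psychological criterion | Proportion | Intervention criteria section | Abstract and aims |
|---|---|---|---|---|
| yes | yes | a | fulfils | fulfils |
| yes | no | b | fulfils | does not fulfil |
| no | yes | c | fulfils | does not fulfil |
| no | no | d | does not fulfil | does not fulfil |

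The rules agree on two cells and disagree on two. The proportion fulfilling the criteria is a + b + c under the written rule and a under the abstract and aims. The ineligible comparison group is d under the first and b + c + d under the second. The group that meets the criteria but refuses after allocation (group 3 in Study I, group 4 in Study II) changes in the same way. So does the comparison of participants with eligible nonparticipants planned under Intention to treat analysis.

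**2. Size.** The proportion of those fulfilling the written rule who fall outside the stated population is (b + c) / (a + b + c). The article gives none of a, b or c, and no joint or marginal prevalence, so this proportion cannot be evaluated.

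**3. The plan's own figures.** These were checked to see whether any depends on the rule.

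- Study I. Inputs from Power calculations: difference 1.4, SD 2.8, power 80 %, level 0.05 (taken as two-sided). With the normal approximation, n per arm = 2 × (1.96 + 0.84)² × (2.8 / 1.4)² = 2 × 7.84 × 4 = 62.7, so 63. The exact t test gives 63.8, so 64, as stated. With 21 per arm, power is 36.7 % by the normal approximation and 35.3 % by the t test. The stated figure is 37 %.
- Study II. With two equal means and a third differing by 1.4, f = (1.4 / 2.8) × √(2/9) = 0.236. The ANOVA needs 59 per arm, and 60 gives 80.8 %. Then 60 × 1.15 = 69, against the stated 70.

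The figures reproduce to within rounding. None of them takes the eligibility rule as an input, so none changes with the reading chosen.

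**4. Does any other text support the alternative reading?** The Discussion says that some patients were not depressed at inclusion. That fits both rules, because under the joint rule a patient can qualify through anxiety, alexithymia or self-image. Nothing in the available text outside the Intervention criteria section supports treating the two conditions as alternatives.

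**The case against.** The strongest reply is that this is a slip in one sentence. Every other description of the population requires both conditions, and the section defers to Fig. 1, whose caption says that it describes the criteria for randomisation and allocation. That may be right, and it means that nothing here shows a deliberate choice of an either/or design. It does not remove the contradiction. If the figure requires both, the sentence conflicts with the figure that it cites. If the figure says either, it conflicts with the title, abstract and aims.

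A reader might also infer more than the text supports:

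- **That the written rule costs a known amount of power.** This would need an assumed share of non-responders, zero effect in all of them and an unchanged SD of 2.8. The article supplies none of these. The depression cut-off is 8 points (Self-report instruments), so a patient scoring from 2 to 7 still has room for a 1.4-point fall. The Discussion argues that a reduction may be worthwhile in patients below the cut-off. The joint rule would also admit some patients with low depression scores, and patients with a psychological criterion but HbA1c below the cut-off need not dilute the depression outcome at all.
- **That Study II centres would apply different rules.** The article has nurses recruit and check exclusions, and an independent statistician randomise coded patients. It does not say that centres apply the intervention criteria.
- **That ineligible patients were randomised in Study I.** The article does not show which rule was used.

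**Conclusion.** The point holds as an internal contradiction in the eligibility rule. Two of the four possible patient types are randomised under the Intervention criteria section but are ineligible under the abstract and aims. The contradiction rests on wording alone and needs no assumption about prevalence or effect. Its practical size is unknown, because the article does not give the share of patients meeting only one condition and does not show the rule applied in 2009. It is not evidence of a chosen design, of a quantified loss of power, or of wrong patients having been randomised. It still needs correction before Study II opens, because it governs who is randomised and who becomes a comparator.

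**What to change.** Reconcile the Intervention criteria section and Fig. 1 with the abstract and aims before Study II opens. If the population in the title and aims is meant, replace the either/or wording with: HbA1c of at least 62.5 mmol/mol and at least one of depression, anxiety, alexithymia or a negative self-image. If the alternatives are meant, the title, abstract, aims, design and summary need to say so.

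For Study I, state which rule was applied in 2009 and report, by arm, how many randomised patients met only the HbA1c condition and how many met only the psychological condition.

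The text change is one sentence and a check of one figure. The Study I counts can be tabulated from data collected at baseline. The joint rule gives a smaller eligible pool than the either/or rule (a instead of a + b + c). That matters because the Discussion already foresees recruitment difficulties, but the abstract already implies this smaller pool.
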